## Methods

### Objectives

The proposed study is designed to evaluate whether cholecalciferol substitution in vitamin D deficient kidney transplant recipients has beneficial effects upon the post-transplant outcome compared to placebo. As a primary outcome we will evaluate the impact of cholecalciferol on

- graft function (analyzed using glomerular filtration rate calculated with the MDRD formula as well as albuminuria) one year after kidney transplantation

- the incidence of acute rejection episodes within the first year after kidney transplantation, and

- the frequency and severity (analyzed by means of C-reactive protein levels) of infections within the first year after kidney transplantation.

As a secondary objective we will assess whether cholecalciferol substitution influences the common decline of bone mineral density within the first year after kidney transplantation [44] analyzed by means of absolute bone mineral density (g/cm^2^).

Moreover, courses of calcium levels will be observed in order to assess the safety of cholecalciferol administration at 6800 International Units (IU).

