### Study population and sample size

The study sample will consist of 200 kidney transplant recipients found to be vitamin D deficient (25-hydroxyvitamin D_3 _< 50 nmol per liter) with 100 subjects in each study group. Inclusion and exclusion criteria are detailed in the Appendix. The recruitment phase will last approximately four years with a follow-up period of one year for each subject. A flowchart of the VITA-D study is shown in Figure 1. The sample size calculation was performed according to the following assumptions: Based on the Vienna General Hospital database we concluded that the mean serum creatinine level one year after transplantation is x_1 _= 1,9 mg per deciliter with sigma, the common standard deviation, estimated to be σ = 0.5. An expert panel evaluated that a difference in serum creatinine levels of 0,2 mg per deciliter would represent a significant clinical improvement for the patient. Assuming that α = 0.05 and the power = 0.80 a sample size of 99 for each sample was calculated.

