#### Treatment in hospital

Kidney transplant recipients are treated in hospital between two and four weeks on average. Within this time period blood samples are taken daily as a matter of routine, including analyses of serum creatinine, C-reactive protein levels and calcium levels.

The first DXA (dual energy X-ray absorptiometry) analysis will be performed within the first four weeks after transplantation depending on postoperative complications. However, we aim at performing it within the first two weeks.

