### Statistical analysis

Baseline data will be expressed as mean values ± standard deviation for symmetrically distributed continuous variables, as median and 25th and 75th percentiles for asymmetrically distributed continuous variables, and as absolute and relative frequency for categorical variables.

Serum creatinine values after one year (the primary endpoint) will be compared between the groups by analysis of covariance (ANCOVA), taking into account as covariates creatinine value at randomization, 25-hydroxyvitamin D_3 _at baseline, and variables which, despite randomization, exhibit large group differences at baseline. ANCOVA will also be applied to the area under the curve of repeated measurements on serum creatinine, CRP, and bone mineral density during the first year of follow-up, using the same set of covariates. Categorical variables (number of acute rejection episodes and infections within the first year after transplantation) will be analyzed using χ^2^-test or fisher's exact test, as appropriate.

All analyses will be performed using an "efficacy subset analysis". Patients are included in this analysis if the study medication has been administered for more than seven days.

Moreover, courses of calcium levels will be described. Furthermore, the Bonferroni-Holm correction will be performed to preserve the global significance level of 5%.

Statistical analysis will be performed with SPSS.

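### The bone mineral density analysis inherits the creatinine covariates and does not prespecify the first DXA as a covariate, which costs precision for the secondary objective

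*Protocol article*

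**What the plan says.** The Statistical analysis section compares one-year serum creatinine by ANCOVA and names three kinds of covariate: creatinine at randomization, baseline 25-hydroxyvitamin D3, and variables that turn out to differ markedly between groups at baseline. It continues: "ANCOVA will also be applied to the area under the curve of repeated measurements on serum creatinine, CRP, and bone mineral density". The sentence then fixes the period and the adjustment for these models: "during the first year of follow-up, using the same set of covariates".

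The Objectives section asks, as the secondary objective, whether treatment "influences the common decline of bone mineral density within the first year after kidney transplantation", and specifies absolute BMD in g/cm² as the measure.

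Three scans are planned. "The first DXA (dual energy X-ray absorptiometry) analysis will be performed within the first four weeks after transplantation", with two weeks as the target; the others follow at 5 and 12 months. Study treatment starts on day 5 (Study intervention).

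**The concern.** Read as written, the BMD model adjusts for baseline creatinine, which has no evident link to a patient's bone density, and leaves out the first DXA, which is the natural predictor of the later scans. The clause on large group differences does not close the gap. It depends on the data, and it guards against chance imbalance rather than recovering precision.

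An AUC of absolute BMD that is not adjusted for the first scan is dominated by how dense each patient's bones were at the start. That spread is noise for a question about decline. If scans on the same patient are highly correlated, the noise can hide a real effect on bone, and a null result on the secondary objective would then say little. The article states this covariate set outright, so it is not a detail left open for a fuller analysis plan.

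**Working it through.** **The plan's own figure.** The only sample size calculation concerns creatinine: "a difference in serum creatinine levels of 0,2 mg per deciliter would represent a significant clinical improvement for the patient", with "the common standard deviation, estimated to be σ = 0.5". The normal formula gives n = 2 × (1.960 + 0.842)² × 0.5² / 0.2² = 98.1, rounded up to 99 per group. This matches "Assuming that α = 0.05 and the power = 0.80 a sample size of 99 for each sample was calculated" with a two-sided test. It carries no information about BMD, for which the documents give no SD, correlation, effect size or power.

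**Inputs for BMD.** From the protocol: 100 patients per arm, two-sided α = 0.05, and scans at 0.5 (the two-week target), 5 and 12 months. Assumed, because the documents are silent:
- a between-scan correlation r of 0.5 to 0.98, either equal for all pairs or decaying with time so that r is the correlation between the first and last scan;
- an effect that either grows linearly or is complete by month 5;
- creatinine and 25-hydroxyvitamin D3 explain no BMD variance.

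BMD is in SD units. Bonferroni-Holm and missing data are not modelled; both would lower all powers.

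**Formulas.**
- Trapezoid weights over 11.5 months: w = 2.25/11.5, 5.75/11.5, 3.5/11.5 = 0.196, 0.500, 0.304; sum of squares 0.381.
- Share f of the 12-month effect carried by the mean AUC. Linear: 0.500 × 4.5/11.5 + 0.304 = 0.50. Complete by month 5: 0.500 + 0.304 = 0.80.
- AUC variance, equal correlation: r + (1 − r) × 0.381.
- Covariance of AUC and first scan: 0.196 + 0.804r. Its square is subtracted from the variance when the first DXA is a covariate.
- Reference: the 12-month effect δ that gives 80% power for 12-month BMD adjusted for the first DXA, δ = 2.802 × √(2/100) × √(1 − r²).
- Power = Φ(fδ / (SD × √(2/100)) − 1.960), counting only rejections in the true direction.

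**Example, r = 0.9, linear effect, equal correlation.**
- δ = 2.802 × 0.1414 × 0.436 = 0.173 SD; fδ = 0.0864.
- Planned AUC: variance 0.9 + 0.1 × 0.381 = 0.938, SD 0.969. Power = Φ(0.0864/0.1370 − 1.960) = Φ(−1.33) = 9%.
- AUC with the first DXA: variance 0.938 − 0.920² = 0.0925, SD 0.304. Power = Φ(0.0864/0.0430 − 1.960) = Φ(0.05) = 52%.

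**Power (%) where 12-month BMD adjusted for the first DXA has 80%.**

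| r | Planned AUC, linear (equal / decaying) | Planned AUC, full by month 5 (equal / decaying) | AUC + first DXA, linear (equal) | AUC + first DXA, full by month 5 (equal) |
|---|---|---|---|---|
| 0.5 | 31 / 28 | 65 / 59 | 56 | 92 |
| 0.7 | 20 / 19 | 43 / 40 | 54 | 91 |
| 0.8 | 14 / 14 | 30 / 29 | 53 | 90 |
| 0.9 | 9 / 9 | 17 / 17 | 52 | 90 |
| 0.95 | 6.5 / 6 | 11 / 11 | 52 | 90 |
| 0.98 | 5 / 5 | 7 / 7 | 51 | 89 |

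Under decaying correlation, the AUC with the first DXA has 67–71% (linear) and 97–98% (full by month 5).

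**CRP, same omission.** If adjustment for baseline CRP would give 80% power, leaving it out gives Φ(2.802 × √(1 − ρ²) − 1.960), where ρ is the baseline–outcome correlation: 78% at ρ = 0.2, 76% at 0.3 and 68% at 0.5.

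**The case against.** **The size rests on assumptions.** This stands. With r = 0.5 and an effect complete by month 5, the planned analysis still has 59–65% power. A reader might infer that the trial is bound to report no effect on bone; the documents give no correlation or effect size from which that could follow.

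**The measure is what the protocol chose.** The Objectives section specifies absolute BMD, and randomization makes expected baseline BMD equal, so a difference in mean AUC estimates the difference in average change. This also stands: the issue is precision, not bias or a wrong target.

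**The AUC is not the fault.** A reader might blame the AUC itself and want it replaced. The table does not support that. Once the first DXA is a covariate, the AUC is weaker than 12-month BMD under a linear effect (52% against 80% at r = 0.9, equal correlation) but stronger if the effect is complete by month 5 (90% against 80%).

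**CRP is different.** The Objectives section lists it under the primary outcome, as a measure of infection severity, and the power loss is small at low to moderate correlation. One might suspect that daily sampling in hospital overweights the surgical weeks, but an AUC weights by time, not by number of samples. Nor would peak CRP per infection episode be a safe replacement: it conditions on an event after randomization, so a treatment that prevents mild infections could make the remaining ones look more severe.

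**The text may have meant each outcome's own baseline.** Possibly, but it does not say so.

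**Conclusion.** The point holds as a loss of precision in the BMD analysis. The stated covariate set does not include the first DXA unless it happens to be imbalanced, and this omission is the main cause of the loss. Where 12-month BMD adjusted for the first DXA would have 80% power, the planned analysis has roughly 5–30% if the between-scan correlation is 0.8 or more, and about 19–65% if it is 0.5–0.7. Those figures depend on the assumed correlation and on how the effect develops; the direction does not, since the planned analysis fell below the reference in every scenario tried. The treatment comparison itself remains unbiased. For CRP the same omission is minor at low to moderate baseline correlation. The primary creatinine analysis is unaffected, because its own baseline is already a covariate.

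**What to change.** In the Statistical analysis section, replace the shared covariate set by a rule of this kind: each continuous outcome is adjusted for its own baseline value, namely the first DXA value for BMD, CRP at randomization for CRP and creatinine at randomization for creatinine, together with baseline 25-hydroxyvitamin D3. State that the first DXA enters the BMD model whether or not it is imbalanced.

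Choose between the AUC and 12-month BMD before unblinding and give the reason: 12-month BMD if the effect is expected to build up gradually, the AUC if it is expected early. If the AUC is kept, having the first scan both inside it and as a covariate does no harm, because its contribution to the outcome is absorbed by its own coefficient.

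The cost is a change of wording; all three scans are already planned. One small downside should be acknowledged: the first DXA may come as late as week 4, about 28 − 5 = 23 days after treatment starts, so a trace of early effect could be adjusted away. For CRP, expect only a small gain.

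### The bone mineral density analysis inherits the creatinine covariates and does not name first-scan BMD, so the test of the secondary objective is needlessly imprecise

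*Protocol article*

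**What the plan says.** The Objectives section makes bone the secondary question: whether cholecalciferol "influences the common decline of bone mineral density within the first year after kidney transplantation", "analyzed by means of absolute bone mineral density" in g/cm2.

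DXA is planned three times. The first "analysis will be performed within the first four weeks after transplantation depending on postoperative complications", with two weeks as the aim (Treatment in hospital). The others follow at 5 and 12 months.

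The Statistical analysis section first sets out the creatinine model, "taking into account as covariates creatinine value at randomization", then 25-hydroxyvitamin D3 at baseline, then "variables which, despite randomization, exhibit large group differences at baseline". It goes on: "ANCOVA will also be applied to the area under the curve of repeated measurements on serum creatinine, CRP, and bone mineral density", with the covariates carried over unchanged: "bone mineral density during the first year of follow-up, using the same set of covariates".

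First-scan BMD is not named as a covariate. The area is not described as baseline-subtracted or as a change.

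**The concern.** A patient's BMD at month 5 or 12 is mostly the BMD that patient already had at transplantation. The area under absolute values carries that stable component and also includes the first scan itself. The two named covariates, creatinine and 25-hydroxyvitamin D3, can be expected to explain little of it. The one measurement that would remove it is scheduled but left out of the named set.

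At stake is the information value of the only stated secondary objective. If between-patient variation dominates the standard error, a real effect on bone loss is likely to go undetected and a null result says little. A chance difference in starting BMD that is too small to trigger the imbalance clause would also remain in the estimate.

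**Working it through.** **The plan's own figure.** The documents give no sample size, SD or effect for BMD. The creatinine calculation reproduces: n = 2 × 0.5² × (1.96 + 0.842)² / 0.2² = 98.1, rounded up to 99 per arm (two-sided 5%, power 80%). So 99 or 100 per arm is used below.

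**Weights of the area.** With scans at 0.5, 5 and 12 months, the trapezoid area divided by 11.5 months has weights 2.25/11.5 = 0.196, 5.75/11.5 = 0.500 and 3.5/11.5 = 0.304. A difference that grows linearly to D at month 12 enters as 0.50 D if it starts at the first scan, or 0.52 D if it starts at transplantation.

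**Check 1: equal correlation ρ between scans (assumed 0.80 to 0.98).** In units of SD², with Σw² = 0.381:
- variance of the area = 0.381 + 0.619ρ
- covariance with the first scan = 0.196 + 0.804ρ
- residual variance after adjustment = variance − covariance²

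Power is Φ(effect/SE − 1.96) with SE = √(2 × variance/100). Assumed: SD 0.15 g/cm2, D = 0.03, so 0.015 on the area.

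| ρ | Variance, unadjusted | Variance, adjusted | Ratio | Power, area unadjusted | Power, area adjusted | Power, month 12 adjusted |
|---|---|---|---|---|---|---|
| 0.80 | 0.876 | 0.172 | 5.1 | 11% | 40% | 65% |
| 0.90 | 0.938 | 0.092 | 10.1 | 11% | 64% | 90% |
| 0.95 | 0.969 | 0.048 | 20.2 | 11% | 90% | 99.5% |
| 0.98 | 0.988 | 0.020 | 50.6 | 11% | >99% | >99% |

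The opposite tail would add less than one percentage point. The ratio does not depend on the SD. Moving the first scan to four weeks (0.92 months) changes it only to 5.0 to 49.3.

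**Check 2: random starting level plus random linear change.** Assumed: between-patient SD 0.10 to 0.18, SD of 12-month change 0.03 to 0.06, measurement error 0.01 g/cm2, D = 0.025, 99 per arm, both tails counted.
- *As stated.* SD of the area 0.101 to 0.183; SE = SD × √(2/99) = 0.014 to 0.026. The effect on the area is 0.52 × 0.025 = 0.013. Power is 8% to 15%.
- *With the first scan as covariate.* Residual SD 0.0175 to 0.0304; SE 0.0025 to 0.0043. The effect net of what the first scan already carries is about 0.48 × 0.025 = 0.012. Power is 79% to over 99%.
- *Month-12 BMD with the first scan as covariate.* Power is 81% to over 99%.

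The first scan correlates 0.957 to 0.995 with the area in this model, so it sits at the favourable end of Check 1.

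**Chance imbalance.** The SE of the difference in mean starting BMD is SD × √(2/100). For an SD of 0.12 to 0.20 this is 0.017 to 0.028 g/cm2, against an effect on the area of 0.010 to 0.015 for D of 0.02 to 0.03.

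Both checks use a nominal 5% level. Any Bonferroni-Holm step would lower both sides of the comparison.

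**The case against.** **The objective is still answerable.** A reader might infer that an area of absolute values measures level rather than decline, so that the secondary question cannot be answered. The documents do not support that. Allocation is 1:1 at random, expected starting BMD is equal, and a between-arm difference in follow-up level is an unbiased, if diluted, estimate of the effect on decline. This objection stands: the harm is lost precision.

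**There is a safeguard against imbalance.** A reader might also infer that any chance difference in starting BMD goes straight into the estimate. The imbalance clause would bring first-scan BMD in when the difference is large. That stands in part. The clause acts only after the data are seen, and it does nothing for precision when the arms are balanced.

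**The power figures depend on unstated inputs.** It would be too strong to say that even complete prevention of bone loss would usually be missed. Under the Check 2 SDs and the stated covariates, power against a fully prevented loss is 9-19% for a linear loss of 0.03 g/cm2 and 17-44% for 0.05. It is 36-82% for 0.08, and 35-82% for a loss of 0.05 complete by month 5. This stands, and the size must be read as a range.

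**The wording may be shorthand.** The article condenses a fuller plan, the same set might mean each outcome's own baseline, and absolute might only name the unit. Possible, but the text names creatinine and carries that set over. If something else was meant, the sentence needs correcting anyway.

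**The first scan is not a clean baseline.** It may follow the first dose. True, but the planned area already uses that scan.

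**Conclusion.** The point holds as a matter of efficiency. The stated covariate set leaves out first-scan BMD unless a large imbalance appears, and this makes the bone comparison much less precise than the collected data allow. It does not bias the comparison on average, and it does not touch the primary analysis or the sample size.

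The direction is firm: across assumed correlations of 0.80 to 0.98, adjustment cuts the residual variance at least 5-fold. The gain in power is less certain, because the SD, the correlation, the effect size and the linear course are all assumptions. It is large when scans correlate highly and moderate at 0.80. The calculations also assume that creatinine and 25-hydroxyvitamin D3 explain negligible BMD variance.

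The area need not be abandoned. Once the first scan is a covariate, the area and month-12 BMD have similar power in Check 2, and month 12 does better in Check 1 at the lower correlations. Dropping creatinine from the bone model, or replacing the vitamin D value by its stratum, would add little.

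**What to change.** In the Statistical analysis section, give the bone model its own covariate statement: first-DXA BMD at the same site, prespecified and included whatever the observed balance, in addition to baseline 25-hydroxyvitamin D3. Either the area or month-12 BMD may be the outcome, but the choice should be fixed in advance.

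The cost is one sentence, with no new scans, visits or patients. Two small matters need a line each:
- The first scan can fall up to 28 − 5 = 23 days, about three weeks, after treatment starts on day 5. It should be described as a near-baseline value.
- Patients without a first scan need a stated handling. The planned area has the same need, because it uses that scan too.

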**Methods/Design:**

The VITA-D study, a randomized, placebo-controlled, double-blind study with two parallel groups including a total of 200 kidney transplant recipients, is designed to investigate the immunomodulatory and renoprotective effects of cholecalciferol (vitamin D_3_) within the transplant setting. Kidney transplant recipients found to have vitamin D deficiency defined as 25-hydroxyvitamin D_3 _< 50 nmol per liter will be randomly assigned to receive either oral cholecalciferol therapy or placebo and will be followed for one year. Cholecalciferol will be administered at a dose of 6800 International Units daily over a time period of one year.

The objective is to evaluate the influence of vitamin D_3 _substitution in vitamin D deficient kidney transplant recipients on the post-transplant outcome. As a primary endpoint glomerular filtration rate calculated with the MDRD formula (modification of diet in renal disease) one year after kidney transplantation will be evaluated. Incidence of acute rejection episodes, and the number and severity of infections (analyzed by means of C-reactive protein) within the first year after transplantation will be monitored as well. As a secondary endpoint the influence of vitamin D_3 _on bone mineral density within the first year post-transplant will be assessed. Three DXA analyses will be performed, one within the first four weeks post-transplant, one five months and one twelve months after kidney transplantation.

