### Randomization and blinding

If all inclusion and none of the exclusion criteria are met and informed consent has been obtained kidney transplant recipients will be included in the study and allocated a randomization number according to a randomization list. Thus, the participant will be randomly allocated to one of the two treatment arms. The random allocation sequence will be computer-generated using the Randomizer for Clinical Trials 1.7.0 developed at the Institute for Medical Informatics, Statistics and Documentation, Medical University of Graz, Austria. Block randomization will be used in order to prevent imbalanced treatment group sizes. We will use blocks of six to which the two treatment modalities will be randomly allocated in the ratio 1:1. To ensure homogenous treatment groups randomization is stratified by 25-hydroxyvitamin D_3 _levels, with one sub-stratum of kidney transplant recipients found to have 25-hydroxyvitamin D_3 _levels between 25 and 50 nmol per liter and another of kidney transplant recipients with 25-hydroxyvitamin D_3 _levels below 25 nmol per liter.

Participants, investigators, and outcome assessors will be blinded to the allocated treatment. Blinding will be ensured by the use of investigational products that are identical in packaging, labeling, appearance, smell, and taste. Unblinding will only occur in case of emergency and at the conclusion of the study. In most cases, however, discontinuing the treatment should be sufficient without the need for unblinding. Access to the randomization list is restricted to the pharmacist involved in the study and a research assistant.

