### Study intervention

Kidney transplant recipients found to have 25-hydroxyvitamin D_3 _levels below 50 nmol per liter and who fulfill all of the inclusion and none of the exclusion criteria will be randomized to receive either oral cholecalciferol therapy (Oleovit^® ^D_3_-drops) or a placebo solution. Treatment starts on day five after kidney transplantation. Cholecalciferol will be administered at a dose of 6800 IU daily over a time period of one year.

The only adverse drug reaction caused by vitamin D_3 _that may occur is the rise in blood levels of calcium. In case of hypercalcemia the dose can be reduced immediately as serum calcium levels are monitored routinely at close intervals (daily within the postoperative hospitalization, i.e. between two and four weeks on average, thereafter weekly until the fourth month after transplantation, and subsequently every two to four weeks depending on post-transplant complications). At serum calcium levels > 2,65 mmol per liter vitamin D_3 _administration will be reduced to 3600 IU per day. If calcium levels persist above 2,85 mmol per liter over a period of four weeks vitamin D_3 _administration will be discontinued and restarted when serum calcium levels declined to ≤ 2,65 mmol per liter with only 3600 International Units per day. If calcium levels remain high this may be attributed to a persistent or transient hypercalcemia due to hyperparathyroidism as transient hypercalcemia is observed in 20–50% in kidney transplant recipients. Thus, the subject will be tested with ultrasound and ^99m^Tc-methoxyisobutyl isonitrile (MIBI) scan. However, these subjects will not be excluded from the study.

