#### Day 1–5

If a kidney transplant recipient is found to have 25-hydroxyvitamin D_3 _levels below 50 nmol per liter information about the VITA-D study, its purpose, putative benefits, and possible risks will be given to the patient and he/she will be invited to participate in the trial. All subjects will be informed that the participation in the trial is voluntary and that the subject may refuse to participate or withdraw from the trial at any time without giving reasons, without loss of benefits. Kidney transplant recipients who do not agree to participate in the study will receive standard care.

Demographic and baseline data will be collected of all participants within the first five days after transplantation (gender, age, body mass index, cause of end stage renal disease, mode of renal replacement therapy, duration on dialysis).

#### Day 5

Kidney transplant recipients who agreed to participate in the study will be randomized to receive either oral vitamin D_3 _therapy or placebo.

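### A chi-square or Fisher test on the number of infections does not match the objective of infection frequency and, read at patient level, gives up power

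*Protocol article*

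**What the plan says.** In the protocol article, Statistical analysis deals with the event outcomes in one sentence: "Categorical variables (number of acute rejection episodes and infections within the first year after transplantation) will be analyzed using" a chi-square test or Fisher's exact test, as appropriate. It does not say whether the unit is the patient or the episode, or how a number becomes a category.

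The aims are worded differently for the two outcomes. For infections, Objectives has "the frequency and severity (analyzed by means of C-reactive protein levels) of infections within the first year after kidney transplantation", and the Abstract says that "the number and severity of infections (analyzed by means of C-reactive protein) within the first year after transplantation will be monitored as well". For rejection, Objectives has "the incidence of acute rejection episodes within the first year after kidney transplantation, and", and the Interims analysis section also speaks of incidence.

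Severity of infection has its own analysis, an ANCOVA of the area under the CRP curve. Nothing else in the section measures how often patients are infected.

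Two design features also bear on the analysis. Randomisation is stratified at 25 nmol per liter of 25-hydroxyvitamin D ("To ensure homogenous treatment groups randomization is stratified by 25-hydroxyvitamin D_3 _levels"). Randomisation and the first dose fall on day five ("Treatment starts on day five after kidney transplantation"), whereas the event window opens at transplantation.

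**The concern.** The number of infections in a patient's first year is a count, and the objective asks how often infections occur. A contingency-table test can be applied to such data in three ways:

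- **Ever/never per patient.** Valid, but a patient with one infection and a patient with five are treated alike, so frequency is lost.
- **Patients classed 0, 1, 2, 3 or more.** Valid and keeps repeat infections, but the test ignores the order of the classes and spends three degrees of freedom.
- **Episodes as the unit.** Repeat infections in one patient are treated as independent. If some patients are more prone to infection than others, the variance is understated and the test is anticonservative.

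On the first two readings, a real reduction in infections may be missed. On the third, a false positive is more likely than 5%, and the Bonferroni-Holm correction does not help because it needs valid p-values to start from. The protocol names a test for this outcome, so this is not simply a detail left to a fuller document.

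**Working it through.** **The plan's own figure.** The sample size is for serum creatinine: n = 2(1.96 + 0.8416)² × 0.5² / 0.2² = 98.1, rounded up to 99 per group. The stated figure is reproduced, but it says nothing about infections. Only the 100 per arm carries over.

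**Assumptions.** The documents give no event rates. Counts per patient are taken as negative binomial with mean μ per patient-year and dispersion k (variance μ(1 + kμ)), complete one-year follow-up, and a rate ratio of 0.65 under the alternative. The infection-like range is μ = 1.0 to 2.0 with k = 0.5 to 1.0. A mean of 0.3 stands for a rarer outcome such as rejection.

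**Ever/never, worked for μ = 1, k = 1.** The proportion with any infection is 1 − (1 + kμ)^(−1/k). Control: 1 − 1/2 = 0.500. Treated (μ = 0.65): 1 − 1/1.65 = 0.394. The difference is 0.106, with standard error 0.0703 under the null and 0.0699 under the alternative. Power = Φ[(0.106 − 1.96 × 0.0703)/0.0699], about 33%.

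**Rate comparison, same setting.** Variance of the log rate ratio = [(1/μ₁ + k) + (1/μ₂ + k)]/100 = [(1 + 1) + (1.538 + 1)]/100 = 0.0454, so SE = 0.213. |ln 0.65| = 0.431, and 0.431/0.213 = 2.02. Power = Φ(2.02 − 1.96), about 53%.

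**Simulated power at rate ratio 0.65** (2,000 trials per setting; the rate comparison uses a robust variance):

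| μ | k | ever/never | 0/1/2/3+ | rate comparison |
|---|---|---|---|---|
| 0.3 | 0.5 | 25% | 16% | 28% |
| 0.3 | 1.0 | 23% | 15% | 27% |
| 1.0 | 0.5 | 44% | 42% | 62% |
| 1.0 | 1.0 | 36% | 34% | 54% |
| 2.0 | 0.5 | 43% | 55% | 81% |
| 2.0 | 1.0 | 33% | 40% | 69% |

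A separate set of 4,000 trials per setting gave, for ever/never against rate, 33% v 53% (μ = 1.0, k = 1), 35% v 61% (μ = 1.5, k = 1) and 45% v 74% (μ = 1.5, k = 0.5). Across both sets, for means of 1.0 to 2.0, the patient-level tests have about 33-55% power and the rate comparison about 53-81%.

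**Type I error, patient-level tests.** Simulated: 4.8-5.8% for ever/never and 3.5-5.4% for 0/1/2/3+. Both are close to or below nominal.

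**Type I error, episodes as unit.** The test understates the variance by the factor 1 + kμ, so the true level is 2[1 − Φ(1.96/√(1 + kμ))]:

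- μ = 1, k = 1: factor 2.0, about 17% (simulated 16.7%).
- μ = 1.5, k = 1: factor 2.5, about 21% (simulated 21.7%).
- μ = 1.5, k = 0.5: factor 1.75, about 14% (simulated 13.6%).

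Across means of 0.3 to 2.0, the 2,000-trial simulation gives 6.8% to 24.8%, that is, about 7-25%.

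**Days before randomisation.** 5/365 = 1.4% of the window. If a share f of events falls there, a true rate ratio of 0.65 becomes f + (1 − f) × 0.65: 0.655 at f = 1.4%, and 0.685 at f = 10%. For an assumed 30% v 15% of patients with an event, power falls from 0.72 to 0.71 and 0.62 respectively.

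**The case against.** The strongest reply is that the section speaks of categorical variables, in an analysis set defined by which patients are included. That points to one category per patient, and such a test holds its level. This stands. A reader might infer that the planned test has a false-positive rate several times nominal, but the text nowhere makes episodes the unit, so that figure is conditional on the less natural reading. Nor can it be said flatly that repeat infections are ignored, because a 0/1/2/3+ classification keeps them. What remains on the patient-level readings is lost power and a mismatch with the objective.

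A reader might also extend the criticism to rejection. The documents do not support that. The aim there is incidence, which a patient-level two-by-two comparison answers, and at a mean of 0.3 it costs little (23-25% power against 27-28%).

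Three further charges are tempting but minor:

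- **Stratum.** Leaving it out of the test usually makes the test slightly conservative, not invalid.
- **Time at risk.** One year of follow-up is planned for every subject, and handling of death and withdrawal is commonly left to a fuller document. A distortion can be produced (9.4% rejections for ever/never against 6.0% for a rate analysis, at mean 2.0 and dispersion 0.5 with no treatment effect), but only by assuming 5% v 20% early exit.
- **Days before randomisation.** These events cannot depend on allocation, so they dilute and do not bias. More than slight dilution needs early clustering of events, on which the documents give no data.

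Finally, the point should not lean on infections being a primary outcome. Objectives lists them so, but the Abstract names GFR as the primary endpoint, and the sample size and Statistical analysis sections rest on creatinine.

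**Conclusion.** The point holds for infections. The planned test answers a different question from the stated one, and its unit is not fixed. On the natural, patient-level readings it is valid but weak: about 33-55% power against about 53-81% for a rate comparison. Only with episodes as the unit is the level wrong, at about 7-25% in place of 5%.

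All these figures rest on assumed means, dispersions and a rate ratio of 0.65, none of which the documents supply. The direction is firmer than the size: with infections this frequent, every setting examined favours the rate comparison. This is a change the sponsor should make; it is not a flaw that invalidates the trial.

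**What to change.** **Infections.** Replace the chi-square or Fisher test by a negative binomial regression (or Poisson regression with robust variance) of the number of infections per patient. Use treatment and the 25-hydroxyvitamin D randomisation stratum as terms and log follow-up time from randomisation as offset. Report the rate ratio with its 95% confidence interval, and state that the patient is the unit of analysis.

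**Rejection.** Keep a patient-level comparison, and say that the variable is the proportion of patients with at least one episode. Stratifying by 25-hydroxyvitamin D (Cochran-Mantel-Haenszel) is optional.

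**Window.** Counting events from randomisation on day five is a small refinement that avoids slight dilution.

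**Cost.** A few sentences of analysis text, agreed before unblinding, a distributional assumption for the count model, and slightly more analysis work with standard generalised linear model procedures. No new data and no additional patients are needed.
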